### **7.3 Follow-up of serious adverse events**

All SAEs related to the intervention will be followed until they have abated, or until a stable situation has been reached. Depending on the event, follow up may require additional tests or medical procedures as indicated, and/or referral to the general physician or a medical specialist.

SAEs need to be reported till end of study within the Netherlands, as defined in the protocol

### **7.4 Data Safety Monitoring Board (DSMB) / Safety Committee**

Not applicable, as both study interventions are common procedures in the Netherlands.

**8. STATISTICAL ANALYSIS**

Descriptive analysis will be performed to compare baseline characteristics between the patients treated using the PLA and DLA. We will use generalized estimating equations (GEE) for longitudinal analysis on an intention-to-treat and additional per-protocol basis to investigate the effect of surgical approach. All analyses will be done using the Statistical Package for the Social Sciences (SPSS, Chicago, Illinois, USA).

**8.1 Primary study parameter(s)**

In the primary GEE model, the primary outcome variable studied (health related quality of life on EQ-5D) will be analyzed as a dependent variable, using treatment allocation (DLA vs. PLA) as between subjects' variable and time as within subjects' variable. In a similar way, continuous secondary outcome variables will be analyzed using similar GEE models. All models will assess the interaction term of group and time, to evaluate whether the change over time differed between PLA and DLA.

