#### 4.4 Sample size calculation

We based our sample size calculation on a superiority design. As stated before the EQ-5D will serve as primary outcome measure. We have used the results from earlier studies on this subject for our sample size calculation(17–19). For the sample size calculation, we hypothesized that the EQ-5D will be higher in the PLA group. Using a two-sided significance level ( $\alpha$ ) of 0.05 and a power ( $\beta$ ) of 80% with a standard deviation (SD) of 0.3 and a minimal clinical important difference (MCID) of 0.08 (derived from the study mentioned before) a total of 222 subjects are needed in each treatment arm. Taking into account a 25% loss to follow-up after six months, a total number of 610 participants are needed in this superiority design.

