### **Baseline assessment**

At baseline we will assess the EQ-5D-5L, the ADL functionality (KATZ), pre-mobility score and the living status using the Dutch Hip Fracture Audit (DHFA) registration. The assessment of the above outcomes is based on the health status prior to the trauma.

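### The primary GEE uses baseline EQ-5D at most as a repeated response and not as a covariate, which loses precision for the 6-month comparison

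*Protocol*

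**What the plan says.** Protocol section 6.1.1 places the primary outcome, EQ-5D-5L, at 6 months after surgery. Under the Baseline assessment heading of section 6.4 the plan states: "At baseline we will assess the EQ-5D-5L, the ADL functionality (KATZ), pre-mobility score and the living status". The same paragraph says that these values describe health before the injury. The Follow-up data collection text in 6.4 schedules EQ-5D-5L at baseline, 3 and 6 months.

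Section 8.1 takes EQ-5D as the dependent variable of the primary GEE, "using treatment allocation (DLA vs. PLA) as between subjects' variable and time as within subjects' variable". It adds a group-by-time interaction to all models, to judge whether the two approaches differ in how the outcome changes. Continuous secondary outcomes get similar models. No baseline covariate is named for any effectiveness model. Section 8 uses baseline characteristics only for a descriptive comparison.

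Section 4.4 sizes the trial on "a standard deviation (SD) of 0.3 and a minimal clinical important difference (MCID) of 0.08", and concludes that "a total of 222 subjects are needed in each treatment arm".

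**The concern.** Section 8.1 does not say whether baseline is one of the levels of time. The visit schedule and the reference to change suggest that it is. Baseline EQ-5D is then a response in the model, and there are two plausible readings of the primary contrast:

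- **Reading A:** the PLA-DLA difference at 6 months, taken from the group-by-time model. With complete data this is the raw arm difference, and baseline contributes nothing to it.
- **Reading B:** the interaction between baseline and 6 months, which is the difference in change from baseline. Baseline is used, but it is subtracted in full whatever its correlation with the outcome.

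Neither makes the best use of a value that is already planned. At stake are a wider interval and lower power on the primary endpoint. Chance baseline imbalance between the randomised arms is ignored under A and generally over-corrected under B.

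**Working it through.** **Inputs.** From Protocol 4.4: two-sided alpha 0.05, power 80%, SD 0.3, difference 0.08, 222 evaluable per arm. The correlation rho between baseline and 6-month EQ-5D is not in the protocol, so it is assumed and shown as a range. The SD is taken as equal at the two times, and patients as independent.

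**The plan's own figure.** The normal approximation for two means gives 221 per arm, and the noncentral t version gives exactly 222. The stated figure reproduces for an unadjusted 6-month comparison.

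**Variances.** Let D6 and D0 be the arm differences at 6 months and at baseline. All three analyses estimate D6 − b × D0, with variance

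(2 × SD² / n) × (1 + b² − 2 × b × rho).

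- Reading A, b = 0: factor 1.
- Reading B, b = 1: factor 2(1 − rho).
- Baseline as covariate, b = rho: factor 1 − rho², the minimum over b.

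The covariate-to-change variance ratio is (1 − rho²) / [2(1 − rho)] = (1 + rho)/2. This is below 1 for every rho below 1, and 1 − rho² is below 1 for every rho above 0. The covariate model is therefore the most precise of the three for any rho between 0 and 1.

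**Numbers at 222 per arm.** For the raw contrast, SE = 0.3 × sqrt(2/222) = 0.0285. Then 0.08/0.0285 = 2.81, and power = Phi(2.81 − 1.96) = 80.2%. The other entries multiply this SE by the square root of the factor.

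| rho (assumed) | A: raw 6-month contrast | B: change from baseline | Baseline as covariate | SE, covariate |
|---|---|---|---|---|
| 0.1 | 80.2% | 55.3% | 80.6% | 0.0283 |
| 0.3 | 80.2% | 66.1% | 83.8% | 0.0272 |
| 0.5 | 80.2% | 80.2% | 90.0% | 0.0247 |
| 0.7 | 80.2% | 95.2% | 97.6% | 0.0203 |

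Equivalently, the covariate model reaches 80% power with 219, 201, 166 and 113 per arm at these values of rho (normal approximation).

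**Simulation check.** GEE was run on 300 simulated trials with 222 per arm, rho 0.5 between all visits and complete data. The SD of the 6-month contrast from the group-by-time model was 0.0290, identical to a model that left baseline out. It was 0.0287 for the interaction and 0.0249 with baseline as covariate. This agrees with the formulas (0.0285, 0.0285 and 0.0247).

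**The case against.** **Covariates belong in the SAP.** Section 8.1 does not say that its terms are the only ones, and the SAP is not shown. In part this stands, since a SAP could add baseline. But 8.1 does specify the primary model, and as written it points to a less efficient analysis. The criticism is of that stated model and not of missing detail.

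**Baseline is already used.** On Reading B it is, and a reader who took the model to contain only treatment and time would overlook the interaction. At rho 0.7 the gain over Reading B is 2.4 points (97.6 − 95.2), far less than the 17.4 points over Reading A (97.6 − 80.2). Below rho 0.5, however, Reading B does worse than ignoring baseline. The covariate model beats both.

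**Rho is unknown and may be low.** This stands. Baseline is recalled pre-injury health, and 6.1.1 allows proxy rating. Either could weaken the correlation, and nothing in the protocol shows that it is strong.

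**Baseline is neither complete nor free.** A reader might infer that every patient has a usable value at no cost. The protocol does not support that. Time before surgery is short. Section 6.4 describes randomisation ahead of the baseline assessment, with no rule that baseline precedes allocation, and 6.2 says patients are not blinded. In the natural experiment (6.3) consent follows surgery, so recall may post-date treatment. The recommendation is therefore limited to the randomised patients.

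**Conclusion.** The point holds as one of efficiency. For any rho between 0 and 1, the model in 8.1 gives a less precise 6-month comparison than one with baseline EQ-5D as covariate, under either reading of the primary contrast. Over the raw contrast the power gain is 0.4 points at rho 0.1, 3.6 at 0.3, 9.8 at 0.5 and 17.4 at 0.7. Over the interaction it is 17.7, 9.8 and 2.4 points at rho 0.3, 0.5 and 0.7. These sizes rest on an assumed rho, equal SDs, independent patients and complete data.

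A reader might infer that the sample size is wrong or the trial underpowered. The documents do not support this for the unadjusted 6-month comparison, for which 222 per arm is correct. Power would fall below 80% only if the change-from-baseline interaction were the primary test and rho were below 0.5. The protocol settles neither condition.

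**What to change.** In section 8.1, for the randomised patients, take 3- and 6-month EQ-5D as the repeated response. Include baseline EQ-5D and baseline by time as covariates, alongside treatment, time and treatment by time. Name the adjusted 6-month PLA-DLA difference as the primary estimate. An equivalent option keeps baseline as a response but constrains its mean to be equal in both randomised arms, which retains patients without a baseline value. Treat KATZ and mobility likewise, with their own baseline values, where they are analysed as continuous.

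The analysis change takes a sentence or two and needs no new data item or visit. There are three small costs:

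- Missing baseline values need a simple imputation under the covariate version.
- The recalled pre-injury value should be recorded before the allocation is known. Section 6.4 should say so, and this may need a small change in procedure.
- Any baseline adjustment in the natural experiment should carry the caveat that the value may have been recalled after treatment.

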### **6.2 Randomisation, blinding and treatment allocation**

Eligible patients admitted to the hospitals where both surgical techniques are practiced, are invited for participating in our RCT prior to the surgery. When patients agree to participate, written informed consent will be obtained and patients will be randomised between the PLA and the DLA. Randomisation will be stratified per center and per orthopaedic/trauma surgeon. Randomisation will be done in CASTOR EDC, a secured study and data management system with built-in randomisation (variable block method).

Surgeons, patients or outcome assessors cannot be blinded since the different surgical approaches are easily distinguishable (i.e. based on the location of the scar).

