### **Randomisation**

After obtaining informed consent at the emergency department or patient ward, patients will be randomly assigned in a 1:1 allocation ratio to one of the following study arms:

- Treatment with a cemented hemiarthroplasty using the DLA
- Treatment with a cemented hemiarthroplasty using the PLA

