**8.3 Cost-effectiveness analyses**

An economic evaluation will be performed from the societal perspective and in accordance with the intention-to-treat principle. All costs and consequences relevant to the intervention will be taken into account. Intervention costs will be estimated using a micro-costing approach. Retrospective cost questionnaires will be administered at 4 weeks, and at 3 and 6 months follow-up to collect data on healthcare utilization (for example visits to general practitioner, physiotherapy, exercise therapy, rehabilitation, social work, medication), the use of informal care, absenteeism, presenteeism, and unpaid productivity losses. Resource use will be valued in accordance with the Dutch manual of costing of the Netherlands Health Institute (Zorginstituut Nederland). Missing data will be imputed using multiple imputation by chained equations(30). Incremental Cost Effectiveness Ratios (ICERs) will be calculated by dividing the difference in costs by that in effects. We will perform a cost-utility analysis with QALYs as outcome. In order to account for the possible clustering of data, analyses will be performed using linear multilevel analyses(31). Accounting for the possible clustering of data (e.g. at the hospital level) is very important, as most economic evaluations fail to do so, whereas

ignoring the possible clustering of data might lead to inaccurate levels of uncertainty and inaccurate point estimates(31). Bootstrapping techniques will be used to estimate the uncertainty surrounding the cost-effectiveness estimates. Uncertainty will be shown in cost-effectiveness planes and cost-effectiveness acceptability curves, and sensitivity analyses will be performed to test the robustness of the study results(32–34).

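### The primary model and the chi-square tests leave out the centre and surgeon strata used in randomisation, which costs a little precision in the RCT but does not inflate false positives

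*Protocol*

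**What the plan says.** Section 6.2 of the Protocol fixes the design: "Randomisation will be stratified per center and per orthopaedic/trauma surgeon", using blocks of varying size. Under the Randomisation heading of section 6.4, "patients will be randomly assigned in a 1:1 allocation ratio".

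Section 8 names the method: "We will use generalized estimating equations (GEE) for longitudinal analysis on an intention-to-treat and additional per-protocol basis". Section 8.1 gives the terms of the primary model: EQ-5D as the outcome, "using treatment allocation (DLA vs. PLA) as between subjects' variable and time as within subjects' variable". It adds: "All models will assess the interaction term of group and time". Neither centre nor surgeon is mentioned. Section 8.2 plans chi-square tests and logistic regression for dichotomous secondary outcomes and names no covariates for either.

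Section 8.3, on the economic evaluation, takes another line: "In order to account for the possible clustering of data, analyses will be performed using linear multilevel analyses". It gives the reason as well: "Accounting for the possible clustering of data (e.g. at the hospital level) is very important, as most economic evaluations fail to do so", and warns that both the uncertainty and the estimates may otherwise be inaccurate.

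**The concern.** Blocked 1:1 allocation within strata balances centre and surgeon between the arms. Whatever part of the outcome variance they explain largely drops out of the treatment contrast. A model without the strata still counts that variance as noise, so the standard error it reports is larger than the true sampling error. Treating the patient as the cluster in the GEE handles repeated measures; it does not correct this.

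The protocol gives grounds to expect some effect of centre and surgeon. Rehabilitation follows each hospital's own protocol, the surgeon chooses the prosthesis, and prophylaxis and wound care follow surgeon judgement and local guidelines (sections 5.1 and 6.4). At stake is efficiency: intervals a little too wide and some power given away, with factors that are already recorded at randomisation. Approach cannot be blinded (section 6.2), which is a further reason to fix the covariates in advance.

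**Working it through.** **Inputs.** Section 4.4 gives a difference of 0.08, SD 0.3, two-sided alpha 0.05, power 80%, 222 per arm. The share of EQ-5D variance due to centre and surgeon together, written r, is not in the protocol; 2, 5 and 10% are assumptions.

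**The plan's own figure.** n per arm = 2 × (1.960 + 0.842)² × 0.3² / 0.08² = 220.7, so 221 by the normal approximation. The t-based calculation gives 222 (power 80.05%), so the stated 222 is reproduced.

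**Contrast between arms at 6 months, assuming balance within strata**

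- SE reported without strata: 0.3 × √(2/222) = 0.0285.
- True SE: 0.0285 × √(1 − r). The reported SE is too large by the factor 1/√(1 − r).
- Type I error without strata: 2 × [1 − Φ(1.96/√(1 − r))].
- Standardised effect: 0.08/0.0285 = 2.81.
- Power without strata: Φ((2.81 − 1.96)/√(1 − r)).
- Power with strata: Φ(2.81/√(1 − r) − 1.96).

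For r = 0.05, √0.95 = 0.975. The SE factor is 1/0.975 = 1.026. Type I error is 2 × [1 − Φ(2.011)] = 4.4%. Power is Φ(0.872) = 80.8% without the strata and Φ(0.922) = 82.2% with them.

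| r (assumed) | SE factor | Type I error | Power without strata | Power with strata |
|---|---|---|---|---|
| 2% | 1.010 | 4.8% | 80.5% | 81.0% |
| 5% | 1.026 | 4.4% | 80.8% | 82.2% |
| 10% | 1.054 | 3.9% | 81.5% | 84.2% |

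**Small strata and dropout.** The closed form assumes perfect balance, so it was checked by simulation: 610 patients, 10 centres with 4 surgeons each (assumed), blocks of 2, 4 or 6, 25% loss, 3,000 runs, r split equally between centre and surgeon.

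- r = 10%: reported SE 0.0280 against a true 0.0269 (about 4% too large). Type I error is 4.0% without the strata and 4.9% with them; power is 81.3% against 83.3%.
- r = 2%: no visible difference (type I error 5.3% against 5.2%, power 80.9% against 81.0%).

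**Group-by-time test with baseline as a time level.** EQ-5D is collected at baseline, 3 and 6 months (section 6.4). A centre or surgeon effect that is constant over time cancels in each patient's change. In a GEE simulation (exchangeable correlation, 480 patients, 40 strata, r = 10%, all of it constant, 100 runs per setting), the mean SE of the 6-month interaction was 0.02581 with and without stratum main effects. With 25% loss at 6 months it was 0.02870 without and 0.02866 with them, a difference of 0.1%. Effects that arise only after surgery do not cancel: if these make up 10% of the variance, the reported SE is about 4% above the true SE.

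**The case against.** The strongest reply is that the protocol does not say these are the only terms and that covariates are commonly settled in the SAP, which is not at hand. That is fair for detail the protocol leaves open. Section 8.1, however, does not defer the model. It states the terms, down to the interaction, and does so without the factors that define the randomisation.

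Second, the tabulated figures are for a contrast between arms at 6 months, whereas section 8.1 describes a test of change over time. This stands as a limit on the size. If baseline is a time level, only effects arising after surgery count, and stratum main effects alone would not help. It does not remove the point: the endpoint is EQ-5D at 6 months (section 6.1.1), baseline refers to health before the trauma (section 6.4), and effects of surgery and local rehabilitation come later.

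Third, the harm is small and conservative. That also stands: power without the strata remains at or above 80% in every row of the table.

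A reader might infer three stronger things that the documents do not support:

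- That false positives are inflated in the RCT. The error runs the other way.
- That sections 8.1 and 8.3 contradict each other, or that the clinical and economic results must disagree without cause. QALYs accumulate over follow-up, and section 8.3 uses multiple imputation, so differences are to be expected. The multilevel plan there may also have the natural experiment in view. What remains is a difference in how hospital structure is treated.
- That section 8.2 lacks a regression. Logistic models are planned; only their covariates are unstated.

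The natural experiment is a separate matter. There the hospital determines the approach, so ignoring hospital would make standard errors too narrow. Sections 8 and 8.1 do not say whether the GEE covers it.

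**Conclusion.** The mismatch between design and stated analysis is real, and it is a modest loss of efficiency in the RCT rather than a threat to validity. For a contrast between arms at 6 months, the standard error is about 1 to 5% too large and 0.5 to 2.7 percentage points of power are lost (81.0 − 80.5 at r = 2%; 84.2 − 81.5 at r = 10%). This rests on assumed variance shares of 2 to 10%, for which the protocol gives no value, and on near balance within strata. At about 2% or below the effect is negligible. Under a group-by-time test that includes baseline, the loss is smaller to the extent that centre and surgeon differences were already present before surgery. The change is worth making because it is cheap and brings the analysis into line with the design.

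**What to change.** In 8.1, state that all RCT models include the stratification factors as fixed covariates (centre, with surgeon strata within it and small strata pooled by a rule set in advance), together with their interaction with time. The time interaction is needed so that the 6-month contrast itself is adjusted.

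Alternatively, replace the GEE with a linear mixed model with centre as a fixed effect and surgeon as a random intercept. A random intercept cannot be added to a GEE, so this option changes the method named in section 8.

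In 8.2, make the planned logistic regression, adjusted for centre, the main analysis of dichotomous outcomes and keep chi-square as descriptive.

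The cost is a sentence or two in each section and matching text in the SAP. No new data are needed, since centre and surgeon are recorded for randomisation. The drawback is that sparse surgeon strata must be pooled.

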## 6.4 Study procedures

|                              | Screening                              | Informed consent procedure       | Baseline assessment | Surgery                                               | 4 weeks follow up              | 3 months follow up                                                              | 6 months follow up                                                              |
|------------------------------|-----------------------------------------------|-----------------------------------------|----------------------------|--------------------------------------------------------------|---------------------------------------|----------------------------------------------------------------------------------------|----------------------------------------------------------------------------------------|
| Clinician/ researcher | Identify eligible patients with hip fractures | Explain PIF, answer questions, sign ICF | DHFA*                      | Record implant details
Record complications               |                                       | Standard clinical follow up, including DHFA                                            | Standard clinical follow up                                                            |
| Researcher            | Identify eligible patients with hip fractures | Answer additional questions if needed   | - DHFA
- EQ-5D          | Screen surgical report for relevant information if necessary | Health care utilization questionnaire | - EQ-5D
- FES-1 scale
- NRS
- SPPB
- Health care utilization questionnaire | - EQ-5D
- FES-1 scale
- NRS
- DHFA
- Health care utilization questionnaire |
| Patient/ proxy        |                                               | Read PIF, ask questions, sign IC        | Complete questionnaire     |                                                              | Complete questionnaire                | - Complete questionnaires
- SPPB at outpatient clinic                               | Complete questionnaires                                                                |

\*DHFA is a registry used in standard care includes: living status, pre-mobility score, KATZ, ASA, complications, discharge destination, re-operations

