### **Follow-up data collection**

The baseline and follow-up assessment will be conducted by the coordinating research team of the OLVG. There are three follow-up moments at 4 weeks, 3 and 6 months postoperative. The primary outcome measurement EQ-5D-5L and the secondary outcomes FES-I scale will be assessed through questionnaires online, by hardcopy or by phone at baseline, 3 and 6 months postoperatively. The health care utilization questionnaire will be assessed at 4 weeks, 3 and 6 months follow-up. The questionnaires will be handed out by the coordinating researcher. Other secondary outcome measurements (e.g. KATZ, mobility score, complications, re-operations) are detailed in the DHFA at baseline and 3 months post-operatively and will be assessed through questionnaires online, by hardcopy or by phone at 6 months after surgery and will be handed out by the coordinating researcher.

The assessment of the Short Physical Performance Battery (SPPB) balance test, which is not included in the DHFA, will be performed by one of the study researchers or nurse practitioner to protect continuity and feasibility and will only be assessed in patients included in the RCT. The SPPB will not be assessed in all patients, but in a subgroup of the patient population because the sample size is smaller. The SPPB is a group of measures that combines the results of the gait speed, chair stand and balance tests.(24)

The follow-up questionnaires will contain:

- Health-related quality of life as measured by the EQ-5D questionnaire. The EQ-5D-5L is a descriptive system of health-related quality of life states consisting of five dimensions (mobility, self-care, usual activities, pain/discomfort and anxiety/depression)(25).
- The Katz Index of Independence in Activities of Daily Living, the Katz ADL, is an instrument to assess functional status as a measurement of the client's ability to perform activities of daily living independently consisting six functions (bathing, dressing, toileting, transferring, continence and feeding)(26).
- The Falls Efficacy Scale-International (FES-I) is a short, easy to administer tool that measures the level of concern about falling during social and physical activities inside and outside the home whether or not the person actually does the activity(27).
- Additionally injuries as a result of falling and other (indication to) re-interventions

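### The blanket group-by-time GEE rule in section 8.1 does not fit the visit schedule for SPPB and NRS pain, and whether it fits FES-I depends on an unresolved baseline

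*Protocol*

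**What the plan says.** Section 8.1 describes the primary GEE for EQ-5D, "using treatment allocation (DLA vs. PLA) as between subjects' variable and time as within subjects' variable". It extends the model: "In a similar way, continuous secondary outcome variables will be analyzed using similar GEE models". It then adds: "All models will assess the interaction term of group and time, to evaluate whether the change over time differed between PLA and DLA".

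Section 6.4 gives the visits:

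- **SPPB.** The researcher row of the schedule lists it in the 3-month column only ("EQ-5D - FES-1 scale - NRS - SPPB - Health care utilization questionnaire"), and the patient row has "SPPB at outpatient clinic" at the same visit. It appears neither at baseline nor at 6 months.
- **NRS pain.** It is listed at 3 and 6 months and not at baseline.
- **FES-I.** The schedule lists it at 3 and 6 months. The Baseline assessment text omits it: "At baseline we will assess the EQ-5D-5L, the ADL functionality (KATZ), pre-mobility score and the living status". The Follow-up data collection text includes a baseline: "secondary outcomes FES-I scale will be assessed through questionnaires online, by hardcopy or by phone at baseline, 3 and 6 months postoperatively".
- **Who has SPPB.** The follow-up text first restricts it to patients in the RCT, then says: "The SPPB will not be assessed in all patients, but in a subgroup of the patient population because the sample size is smaller".

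The secondary objective in section 2 asks whether the posterolateral approach gives better outcomes, balance and pain among them.

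**The concern.** A group-by-time term answers the trial's question when there is a measurement from before surgery: the arms start level, and a treatment effect shows as a difference in change. EQ-5D has such a baseline. SPPB and NRS, as scheduled, do not. For SPPB there is no second visit at all. For NRS, the difference in change between months 3 and 6 is not the question in section 2, which is whether one approach leaves patients better off.

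Balance matters here because it is the protocol's proposed mechanism: abductor damage, then loss of balance, then falls (sections 1 and 9.4). SPPB is the performance-based measure of it. If the SPPB subgroup is a further selection within the RCT, made after surgery at a clinic visit and without blinding (section 6.2), the comparison could be open to selection. The text does not settle whether that is so.

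**Working it through.** **Inputs from the protocol (section 4.4):** two-sided alpha 0.05, power 80%, SD 0.3, difference 0.08, 222 per arm. The standardised difference is d = 0.08/0.3 = 0.267.

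**Reproducing the protocol's own figure.** n per arm = 2 × (1.960 + 0.842)² × (0.3/0.08)² ≈ 221 by the normal approximation; the t-test version gives 221.7, so 222. With 25% loss, 444/0.75 = 592, against 610 stated, which is slightly more generous. The size for EQ-5D reproduces. No size is given for SPPB, NRS or FES-I.

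**Assumptions for what follows.** The EQ-5D values d = 0.267 and n = 222 per arm are borrowed for the secondary outcomes, and the within-patient correlation rho is set at 0.3, 0.5 and 0.7. The protocol gives none of these for pain or FES-I, and the SPPB subgroup may be smaller.

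**SPPB, one visit.** The model columns are intercept, group, time and group × time. With a single visit, time is constant and group × time equals group, so the rank is 2 of 4. Only the intercept and the group contrast can be estimated.

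**NRS, 3 and 6 months.** In SD units:

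- Interaction: SE = √[(2/n) × 2(1 − rho)]
- Group difference at one visit: SE = √(2/n) = √(2/222) = 0.0949
- Group difference averaged over both visits: SE = √[(2/n) × (1 + rho)/2]

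| Test | True effect | rho 0.3 | rho 0.5 | rho 0.7 |
|---|---|---|---|---|
| Interaction | d at both visits | 5% | 5% | 5% |
| Interaction | d/2 at 3 months, d at 6 | 22% | 29% | 44% |
| Group difference, one visit | d | 80% | 80% | 80% |
| Group difference, averaged | d at both visits | 94% | 90% | 86% |

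The first row does not depend on the borrowed inputs: a difference that stays the same makes the true interaction zero, so the rejection rate is alpha. In the second row at rho 0.5, for example, SE = 0.0949 and the interaction is 0.133, a ratio of 1.40, giving 29%. A simulation of 1,000 GEE fits at rho 0.5 with a constant effect gave 4.5% for the interaction, 79.5% for the 3-month contrast and 89.4% for the average.

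**FES-I, two cases.** Without a baseline, the NRS rows apply. With a baseline (no difference at baseline, d at 3 and 6 months), the interaction has 2 degrees of freedom and noncentrality n d²/[3(1 − rho)] = 222 × 0.0711/[3(1 − rho)] = 5.26/(1 − rho), that is 7.5, 10.5 and 17.5. Power is 69%, 84% and 97%.

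**The case against.** The strongest reply is that section 8.1 also puts treatment allocation in the model and nowhere makes the interaction the only or deciding test. The same GEE yields a between-arm contrast at each visit, and for SPPB it simply reduces to a 3-month comparison. Naming the contrast is often left to a statistical analysis plan, which is not at hand.

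Much of this stands. A reader might infer that benefits in balance, pain and fear of falling would be missed; the protocol does not support that, because the group term remains. It is not a complete answer, though. With an interaction in the model, the meaning of the group coefficient depends on how time is coded. The only purpose the section states for these models' interaction is a difference in change, applied to all of them. An analysis plan would have to depart from that rule for SPPB, so this is more than missing detail.

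Two further readings go too far:

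- A reader might infer that the interaction is the wrong test for FES-I. The follow-up text gives FES-I a baseline, and the Summary speaks of secondary outcomes generally at baseline, 3 and 6 months. With a baseline the test is reasonable. The Summary sentence is too general to settle NRS or FES-I, since it also covers outcomes such as re-interventions that have no baseline.
- A reader might infer that SPPB is a convenience sample of patients fit enough to attend. No text says so. SPPB is restricted to RCT patients, and the subgroup sentence can be read as explaining just that restriction. Non-attendance is a plausible risk, not a stated plan.

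**Conclusion.** The point holds in a limited form: a rule stated for all continuous secondary outcomes conflicts with the protocol's own schedule.

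- For SPPB, time and group-by-time cannot be estimated. This follows from the single visit and needs no assumption.
- For NRS as scheduled, the interaction cannot detect a stable benefit (5% whatever its size). A stable benefit could be missed if that test is relied on; a plain between-arm contrast is available from the same model.
- For FES-I, what is established is a contradiction between places in section 6.4, and it decides whether the prescribed test works.
- For the SPPB population, the wording leaves open whether the subgroup is all RCT patients or a further selection, and the smaller sample size it refers to is not given.

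The 22–44% and 69–97% figures are illustrative, because they borrow the EQ-5D difference, SD and n and assume the correlations. The primary outcome is not affected by this point. It should be corrected, as a matter of wording on secondary outcomes.

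**What to change.** - **Section 8.1.** Analyse SPPB by a between-arm comparison at 3 months. Analyse NRS by the between-arm difference at a named visit, estimated from the GEE, with the interaction as supportive only.
- **Section 6.4, FES-I.** Reconcile the schedule table, the Baseline assessment text and the Follow-up data collection text on whether a baseline is collected. If none is collected, use the same between-arm contrast as for NRS.
- **Section 6.4, SPPB.** State that it is done in all RCT patients or, if in fewer, give the number and a rule that fixes the subset before allocation.

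The cost is small: protocol wording and, if a subset is used, SPPB assessors working from a pre-set list. The FES-I and SPPB points should be settled in the protocol, because later analysis cannot recover a baseline that was not collected or undo selective testing.
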